## Introduction

Temporomandibular joint (TMJ) disorders (TMDs) are a broad group of conditions affecting the TMJ, masticatory muscles and surrounding structures, leading to pain and dysfunction of the jaw and the muscles responsible for jaw movement.^1^ Patients with TMDs often present with symptoms, such as limited mouth opening, facial pain, localised facial swelling, malocclusion and facial disharmony, all of which can be severely debilitating and significantly impair daily life.^2^

TMDs affect individuals of all ages, with peak incidence from adolescence to 60 years, and are more common in women.^3 4^ Prevalence estimates range widely, from 5%–15% in earlier studies^5^,^8^ to 30%–50% in more recent reviews.^34 9^,^11^ This discrepancy likely reflects the complex, multifactorial nature of TMDs and the challenges associated with their diagnosis and classification. In addition, advances in diagnostic methods and the use of broader inclusion criteria have likely contributed to higher prevalence estimates in recent years.^3 12^

The first-line treatment for TMDs is conservative, with approaches including patient education, physical therapy, pharmacologic management, occlusal appliances and biofeedback in cases of chronic conditions, often within an interdisciplinary approach addressing physical and psychological factors.^213^,^17^ However, end-stage conditions—such as post-tumour resections, ankylosis, osteoarthritis or congenital and developmental anomalies—may severely impair mandibular function, requiring total joint replacement with alloplastic components for the condylar head and temporal fossa.^18^,^21^ The primary goals of TMJ replacement are pain relief, improved jaw function, corrected occlusion and facial deformities and improved quality of life (QoL).^2 5 14 15 22^

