#### Treatment details

Surgical details to be documented include:

Side (left, right or bilateral).Date and duration of the surgery (minutes).Use of preoperative virtual surgical planning.Implant type (stock or customised implants, brand).Material (mandibular and fossa components).Screws used (normal or back-up/safety), including side (left/right), number, length and diameter.Details of surgical approach as per AO standards (preauricular, retromandibular, submandibular or facelift).^34^Use of intermaxillary fixation (intraoperative or postoperative).Length of hospitalisation (days).Details of antibiotics and steroids.Details of functional rehabilitation (type and duration).Details of the type and frequency of pain medication (if indicated).

If applicable, additional surgical procedures (eg, dental extractions, orthognathic surgery, coronoidectomy, eminectomy, resection, reconstruction, bone or fat grafting, soft tissue flap, hardware removal) will be recorded. If a contralateral TMJ replacement is performed during the study, surgery details will be collected.

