#### Adverse events (AEs)

Since this is an observational registry, only anticipated condition-related, treatment-related or implant-related AEs will be documented from the time of consent onwards. These include fixation failure (implant loosening, breakage or instability), dehiscence of incision, wound infections, neurological-related (facial nerve damage, Frey’s syndrome, sensory disturbances or altered hearing), bleeding, haematoma, swelling, injury to adjacent structures, ankylosis, malocclusion, sensitivity to material, heterotopic ossification, disarticulation, contralateral joint dysfunction, condylar resorption, graft loss, revision surgery and any other AEs that may affect the outcome of the registry.

These events are considered events of scientific interest, that is, events that can clearly be connected to the treatment(s) or the medical condition under investigation and will not require immediate reporting to the local EC/IRB unless they occur at a higher frequency and/or severity than that cited in the literature.

This registry can be considered a minimal-risk study, given that participation poses a very low risk compared with the standard-of-care (routine) procedures.

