#### Covariates

Potentially important covariates (prognostic factors) to include in the analysis are:

Age.Gender.Anxiety/depression.Number of previous surgeries (TMJ-related).Onset of disease.Underlying disease.Use of pain medications.Smoking.Type of implant.Geographic region.Baseline scores.Unilateral/bilateral joint replacement.

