#### Radiological parameters

All images collected according to the local standard of care will be evaluated according to the following postoperative parameters:

Displacement of the ramus component.Fracture of the ramus component.Screw loosening.Resorption/osteolysis of the surrounding bone.Status of bone grafts if used (displaced/resorbed/healed).Presence of ectopic bone.

All images collected per standard of care may be used for further analysis, either on-site or by a central reader. Preoperative image analysis will depend on registry findings.

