### Statistical analysis

Since the objectives of this registry are descriptive and exploratory in nature, no formal hypothesis testing is planned, and all analyses will be exploratory. The planned sample size of 200 patients is based on the estimated number of eligible participants expected to be enrolled during the 2-year recruitment period. Eligible patients who refuse TMJ replacement will be included in the study but excluded from sample size calculations. Depending on the volume and quality of the data collected during the first 2 years, the registry may remain open thereafter, with patient FU of up to 5 years.

A detailed statistical analysis plan (SAP) will be finalised before the final analysis (ie, the analysis from which the results will be summarised in the final registry report). As the primary aim of the current registry is descriptive, patient characteristics, clinical data and outcomes recorded at standard-of-care scheduled FU assessments will be presented using descriptive summary statistics. Categorical variables will be summarised using frequency and percentage for each category. Continuous variables will be summarised using the mean, SD, median, IQR and minimum and maximum values. Analyses will also be stratified by clinically relevant categories, including treatment patterns.

Longitudinal clinical, functional and PRO data may be analysed using mixed-effects models for repeated measures, allowing inclusion of all available data and minimising the impact of missing data. Time-to-event analyses are planned, with survival status recorded at each scheduled FU. Kaplan-Meier methods will estimate survival probabilities, and multivariable Cox proportional hazards models will be used where event numbers permit.

Centre effects and geographic variability will be addressed using multilevel (hierarchical) models with patients nested within regions to account for clustering and differences in practice patterns. For time-to-event outcomes, region (or treating centre) will additionally be included as a covariate in Cox regression models when sample sizes permit. The AEs will be summarised at both patient and event levels, with rates calculated using the total population as the denominator, regardless of dropouts, with 95% CIs provided.

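### For graft loss, contralateral joint dysfunction and condylar resorption, an AE rate over all patients measures burden; an at-risk rate should stand beside it

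*Protocol article*

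**What the plan says.** The Statistical analysis section of the protocol article says AEs will be summarised per patient and per event, "with rates calculated using the total population as the denominator", whether or not patients drop out, and with 95% CIs. It names no exception for any type of event.

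The Adverse events section lists, among others, "disarticulation, contralateral joint dysfunction, condylar resorption, graft loss, revision surgery".

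Other sections show that the structures these events need are not present in everyone:

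- Treatment details records "Side (left, right or bilateral", and the list of covariates includes "Unilateral/bilateral joint replacement". Laterality is therefore expected to vary.
- The Introduction describes end-stage disease as "requiring total joint replacement with alloplastic components for the condylar head and temporal fossa", so a replaced side no longer has its natural condylar head.
- Treatment details lists bone or fat grafting among additional procedures recorded only where they apply. Radiological parameters makes graft assessment conditional: "Status of bone grafts if used (displaced/resorbed/healed".
- Treatment details and a footnote to Table 2 foresee a later replacement of the opposite joint during the study.

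**The concern.** With one denominator for all AEs, patients who cannot have an event still count below the line. A bilaterally replaced patient has no unreplaced opposite joint after surgery, and a patient without a graft cannot lose one. The radiological plan respects this condition for grafts; the AE rule does not. The effect is separate from dropout: it would remain in a patient-level rate with complete follow-up.

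Two uses are at stake. First, a clinician advising a patient who will have one side replaced, or a graft placed, may take the published percentage as that patient's risk. Second, the Discussion says the registry will allow complication rates to be compared. For these AEs, a centre or region that operates bilaterally more often, or grafts less often, would show lower figures with no difference in risk among the patients concerned.

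**Working it through.** The article gives no AE rate, so there is no figure to reproduce. The check shows what the stated rule does.

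**Inputs**

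- N = 200 operated patients (Statistical analysis; patients who refuse surgery are outside this number). I take this as the total population.
- s, the share of patients at risk. It is not given for laterality or grafting, so it is varied.
- p, the true risk among patients who can have the event. It is not given; 10% is assumed for illustration.

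**Formula**

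Events = p × s × N. Planned rate = events / N = p × s. At-risk rate = events / (s × N) = p. The planned rate is below p whenever s is below 1. The direction follows from the rule alone; the size depends on s.

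**Results (p = 10%, Wilson 95% CI)**

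| Share at risk (assumed) | Planned: events/200 | At-risk rate |
|---|---|---|
| 90% | 18/200 = 9.0% (5.8 to 13.8) | 18/180 = 10.0% (6.4 to 15.3) |
| 75% | 15/200 = 7.5% (4.6 to 12.0) | 15/150 = 10.0% (6.2 to 15.8) |
| 50% | 10/200 = 5.0% (2.7 to 9.0) | 10/100 = 10.0% (5.5 to 17.4) |
| 20% | 4/200 = 2.0% (0.8 to 5.0) | 4/40 = 10.0% (4.0 to 23.1) |
| 10% | 2/200 = 1.0% (0.3 to 3.6) | 2/20 = 10.0% (2.8 to 30.1) |

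At a share of 50% or less, the planned interval lies wholly below the assumed 10%. It is a proper interval for burden but not for risk among those who can have the event.

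**Comparison between centres or regions**

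Take two regions with the same 10% risk of contralateral dysfunction among patients with an unreplaced joint, one with 70% of patients unilateral and the other with 50% (assumed). The planned rates are 10% × 0.70 = 7% and 10% × 0.50 = 5%. The 2-point gap comes only from case mix.

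**When a patient is at risk**

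AEs are recorded from consent, and Table 2 collects them at the preoperative visit. Condylar resorption is also a presenting sign under Diagnosis. A patient later replaced on both sides may therefore have a natural condyle for the first part of the AE window. The argument for condylar resorption and contralateral dysfunction thus applies to postoperative events only. A patient with a staged second replacement is at risk until that operation.

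**The case against.** The strongest reply is that events over all patients is a legitimate descriptive quantity. The registry is exploratory, and the article never calls the rate a conditional risk. This stands. A reader might infer that the planned rates and intervals are simply wrong; the document does not support that. They answer a different question.

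A second reply is that the SAP will supply such detail, and that the clause was mainly meant to settle dropout. A denominator left open would indeed be a SAP matter. This one is stated without exception, so a SAP using other denominators for these AEs would have to add to the published rule. The planned stratification and the subgroups for specific questions do not change the AE denominator, and the article names neither laterality nor grafting as a stratum. Laterality is a listed covariate, and hierarchical models are planned for regional differences. Neither is tied to the AE rates, and grafting is not a listed covariate. A reader could recover the at-risk rate by division if event counts and treatment counts are both published, which limits the harm.

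Two stronger readings are also tempting. One is that many patients cannot have these events; the article gives neither the bilateral nor the grafted share, so this is unknown. The other is that bilaterally replaced patients were never at risk of condylar resorption. That fails because AE recording starts before surgery.

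**Conclusion.** The point holds in limited form. For graft loss, postoperative contralateral joint dysfunction and postoperative resorption of a natural condyle, the single denominator gives burden across the cohort. Read as risk, the figure is too low by a factor equal to the share at risk. With an assumed 10% risk and shares from 90% down to 10%, the reported figure runs from 9.0% to 1.0%. Only the direction is certain, because both the risk and the shares are assumptions.

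Three items in a long AE list are affected, in an exploratory registry that already plans to record side and additional procedures. The issue matters mainly for advice to individual patients and for comparing complication rates between centres or regions.

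**What to change.** Keep the overall rate and add to the Statistical analysis section, and to the SAP:

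- For graft loss, the rate is also given among patients who received a graft.
- For postoperative contralateral joint dysfunction and postoperative condylar resorption, the rate is also given among patients with at least one unreplaced joint after the index surgery.
- Each added rate is shown with its number at risk and a 95% CI.
- Patients with a staged contralateral replacement stay in that denominator, and only events before the second replacement count. Alternatively, a time-to-event estimate censored at that replacement is used.
- Preoperative events are tabulated separately, so that numerator and denominator cover the same period.

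Side, additional procedures and later contralateral surgery are already collected under Treatment details, so no new data are needed for these rules. The cost is a few table rows and wider intervals for the added rates: in the half-at-risk example, 5.5 to 17.4 instead of 2.7 to 9.0.

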**Trial registration number:**

NCT03991728.

STRENGTHS AND LIMITATIONS OF THIS STUDYThis is the first prospective, multicentre international registry for total alloplastic temporomandibular joint (TMJ) replacement with up to 5 years of follow-up (FU).The registry will collect high-quality, prospective data on treatment and outcomes from a large cohort of patients undergoing alloplastic total TMJ replacement, providing broader insights into the underlying disease, treatments and outcomes.A limitation of the study is its observational study design, which precludes direct comparison of treatment outcomes across interventions.The extended FU period (60 months) may result in missing data over time.Differences in treatment protocols and reporting standards across participating centres may affect the consistency, quality and comparability of the collected data.

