### Recruitment

A recruitment period of approximately 60 months is planned to enrol approximately 200 patients.

All eligible participants will be informed by a research team member about the registry’s purpose, procedures, duration, risks, benefits, alternatives to participation and data protection. Written ICF must be obtained before the TMJ replacement surgery, unless waived by the local EC/IRB or, in cases of surgery refusal, before data collection. In all cases, consent must be obtained before entering any data into the electronic case report form (eCRF).

All consented patients will be allocated a unique patient number. Each site will maintain an Identification List (IL) linking each patient’s number to their personal information. This IL is kept safe in a locked place at all times. Sites are not allowed to share the IL with any third party, except the sponsor representative, legal authorities and EC/IRB, who may have access to the IL during on-site monitoring/auditing activities.

All eligible and consented patients who underwent alloplastic total TMJ replacement will be followed up within the registry, unless their participation in the study is prematurely terminated.

Participating sites will register patients who refuse alloplastic total TMJ replacement, but these patients will not be followed up unless they choose to undergo alloplastic total TMJ replacement during the enrolment period.

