### Data collection

Patients will be followed up starting approximately 10 days after treatment and then at 3, 6, 12, 24 and 60 months. A summary of the data to be collected at each visit is shown in table 2. Unscheduled visits may occur at any time during the study in case of a medical emergency or if the investigator deems it necessary for patient care. Unscheduled visits will not be documented.

**Table 2 T2:** Study schedule

Assessment parameters	Visit 1	Visit 2	Visit 3*	Visit 4*	Visit 5*	Visit 6*	Visit 7*	Visit 8*
	Screening/preoperative	Treatment day	Postoperative 10 days (±7 days)	3 months (±30 days)	6 months (±45 days)	12 months (±60 days)	24 months (±90 days)	60 months (±90 days)
Patient information/consent	X†							
Eligibility	X†							
Baseline characteristics	X†							
Reason for refusal of TMJ replacement		X‡						
Treatment details§		X						
Pain medication	X†			X	X	X	X	X
Clinical and functional outcomes	X†		X	X	X	X	X	X
PROs	X†		X	X	X	X	X	X
Anticipated treatment or condition-related AEs	X	X	X	X	X	X	X	X
Survival			X	X	X	X	X	X
Image collection	X†		X			X	X	
Radiographical parameters¶			X			X	X	

* All postoperative FU visits within the defined time windows are calculated from the treatment day (ie, day 0).

† Assessment for patients who will undergo TMJ replacement and for patients who refused TMJ replacement.

‡ Only for patients who refused TMJ replacement.

§ For enrolled patients who underwent total TMJ replacement on one side only and have to undergo TMJ replacement on the contralateral side later during the study, details of additional surgical treatment will be collected at any time during the study.

¶ All images are taken according to local standard-of-care (routine) procedures.

AE, adverse event; FU, follow-up; PRO, patient-reported outcome; TMJ, temporomandibular joint.

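### Adverse event rates over the total population regardless of dropouts understate the 60-month risk of late complications

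*Protocol article*

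**What the plan says.** The Statistical analysis section of the protocol article states: "The AEs will be summarised at both patient and event levels". The same sentence then sets the denominator: "rates calculated using the total population as the denominator, regardless of dropouts, with 95% CIs provided". It names no person-time or time-at-risk measure for AEs.

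Other parts of the article bear on this rule:

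- **Length of follow-up.** Under Data collection, visits run from about 10 days to 3, 6, 12, 24 and 60 months. The strengths and limitations box concedes: "The extended FU period (60 months) may result in missing data over time".
- **Dropouts.** Premature termination of participation says that data of terminated participants are censored and kept in the analyses.
- **Time-to-event methods.** Kaplan-Meier and Cox models are planned under Statistical analysis. The text introduces them through survival status, which the Survival section treats as whether the patient is alive.
- **Who is in the study.** Of refusers the article says: "Eligible patients who refuse TMJ replacement will be included in the study but excluded from sample size calculations". The Recruitment section adds that "these patients will not be followed up unless they choose to undergo alloplastic total TMJ replacement during the enrolment period". Total population is not defined.
- **Start of AE recording.** Under Adverse events: "implant-related AEs will be documented from the time of consent onwards".

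**The concern.** A proportion with a fixed denominator treats every patient as observed for the whole period. For a patient who leaves at month 12, events up to month 12 are counted. Anything after that is invisible, and the patient counts as free of later events through month 60. The numerator can only lose events in this way, while the denominator does not shrink. The article's own statement that terminated patients are censored has no effect on such a rate.

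The AE list includes events that can appear years after surgery: implant loosening or breakage, heterotopic ossification and revision surgery. These are the long-term effects the Introduction says are poorly documented. The Discussion also expects the registry to support comparison of complication rates. Under the stated rule, two centres with the same true risk report different rates if their dropout differs, and the one that loses more patients looks safer.

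**Working it through.** **Plan figure.** There is none to reproduce. The article says "The planned sample size of 200 patients is based on the estimated number of eligible participants expected to be enrolled", so the 200 is a feasibility number. It states no AE, dropout or refusal rate. What follows is an illustration under stated assumptions.

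**Direction.** Compare the planned rate with the rate the same patients would give if all were followed to month 60. The denominators are identical. The planned numerator omits events after dropout, so it cannot be larger. This holds whatever the reason for dropout.

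**Size, constant hazards.** Let R be the true 5-year risk and D the proportion lost by 5 years, with dropout unrelated to AE risk. The yearly hazards are l = −ln(1−R)/5 and m = −ln(1−D)/5. The expected crude proportion is

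l/(l+m) × [1 − exp(−5(l+m))], where the bracket equals 1 − (1−R)(1−D).

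With R = 20%, l = 0.0446:

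| D | m | l/(l+m) | bracket | crude rate | relative shortfall |
|---|---|---|---|---|---|
| 10% | 0.0211 | 0.679 | 0.28 | 19.0% | 5% |
| 30% | 0.0713 | 0.385 | 0.44 | 16.9% | 15% |
| 50% | 0.1386 | 0.244 | 0.60 | 14.6% | 27% |

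The relative shortfall hardly depends on R. At 30% dropout, R = 10% gives 8.4% (shortfall 16%) and R = 5% gives 4.2% (16%).

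**Size, late events only.** If event times are spread evenly over years 2 to 5, the crude rate is R times the mean of exp(−mt) over that interval, which is [exp(−2m) − exp(−5m)]/(3m):

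- D = 30%: (0.867 − 0.700)/0.214 = 0.780, so 20% becomes 15.6% (shortfall 22%).
- D = 50%: (0.758 − 0.500)/0.416 = 0.620, so 20% becomes 12.4% (shortfall 38%).

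**Centre comparison.** With the same true risk of 20% and constant hazards, a centre with 10% dropout would report 19.0% and one with 50% dropout 14.6%. The difference is due to follow-up alone.

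**Check of the remedy.** For R = 20% and D = 30%, expected person-years per patient are 0.44/(0.0446 + 0.0713) = 3.79. The rate is 0.169/3.79 = 0.0446 per year, and 1 − exp(−5 × 0.0446) = 20%. Using time at risk recovers the assumed risk when dropout is non-informative.

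**The case against.** **A crude proportion over all treated patients is a common safety summary.** That is so, and it may stay. The problem is that it is the only AE rate the article states for a registry followed to 60 months.

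**Many listed AEs are perioperative.** Bleeding, haematoma, swelling, dehiscence and wound infection mostly occur before much dropout can happen, and events before dropout are counted. This stands: the point concerns late events, not complication rates as a whole.

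**The planned time-to-event analyses might cover AEs.** The article does speak of time-to-event outcomes in general terms and does not exclude AEs. But it never applies these methods to them, and the one sentence on AE rates prescribes the crude rule.

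**The details belong in the SAP.** Handling of missing data is indeed left to it. The AE denominator is not: the article fixes it.

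**With about 200 patients the bias may be smaller than the sampling error.** For a crude 16.9% on 200 patients, a Wilson 95% interval is 12.4% to 22.7%, which still contains 20%. True, but the bias is in a known direction, does not shrink as the registry grows, and differs by centre.

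**Stronger readings are tempting.**

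- *Refusers dilute the rate.* A reader might infer that refusers, who have no operation, sit in the denominator. Taken literally, 20 events would give 10.0% of 200 but 8.0% of 250. The article does not establish this. In Table 2 the dagger marks "Assessment for patients who will undergo TMJ replacement and for patients who refused TMJ replacement", and the AE row carries no dagger, so no AE assessment is scheduled for refusers. The term is undefined, which is an ambiguity and not a stated error.
- *Preoperative disease is pooled with complications.* Recording from consent does not amount to a plan to pool. Pooling would also raise the rates, not lower them.

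**Conclusion.** The rule is wrong as written for late AEs: it understates their 60-month risk whenever patients are lost before month 60, and more so where more are lost. The direction is certain. The size is not, because dropout and AE rates are absent from the article. Under constant hazards and non-informative dropout, the relative understatement is about 5%, 15% and 27% at 10%, 30% and 50% dropout. It is about 22% and 38% at 30% and 50% if events fall only in months 24 to 60. Dropout linked to AE risk could make it smaller or larger.

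A reader might infer that rates could be halved. That needs 50% dropout, events only after month 24 and refusers as 20% of the denominator all at once (12.4% × 0.8 = 9.9% against 20%). The article supports none of these.

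The severity is should-fix: the registry is descriptive and exploratory, tests no hypothesis, and has yet to finalise its SAP.

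**What to change.** Replace the sentence on AE rates along these lines:

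*The AE population is all patients who underwent alloplastic total TMJ replacement. For AEs that can occur late, the cumulative incidence of a first event from day 0 is reported with 95% CI and numbers at risk, with censoring at last contact and death as a competing event. Event-level rates are given per person-time with 95% CIs that allow for repeated events in a patient. The crude n/N is shown as a labelled descriptive column. Events between consent and day 0 are reported separately.*

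The first sentence also settles whether refusers, and other consenting patients who never have surgery, count in the denominator. Perioperative AEs can be left with the crude summary. If dropout may depend on AE risk, a sensitivity analysis is still needed, because censoring methods assume that it does not.

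The cost is a little more analysis, plus AE onset and last-contact dates. The article does not say that onset dates are recorded. Unscheduled visits are not documented, and the last two visits are 60 − 24 = 36 months apart, so for some late events only the visit interval may be known and the analysis should allow for that. Late-event rates will look less favourable than under the present rule.
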